### 3.3.1.2 Macaques/Mother-Infant Transmission Model

These experiments aimed to develop an immune prophylaxis against mother-to-infant HIV transmission. For this purpose a SHIV infection model in neonatal macaques was established mimicking intrapartum and postnatal mucosal virus exposure (Baba TW et al 1994). Experiments of this type were performed under the guidance of [name] from Daner Faber Cancer Research Institute, Harvard University, Boston, Massachusetts; USA. In the mother-to-infant studies C2F5 and C2G12 were tested in combination with other monoclonal antibodies (IgG1b12 or F105, respectively). C4E10 was added in later studies as soon as sufficient quantities of clinical grade material were available. MAb combinations including C4E10 provided better protection upon challenge of neonate macaques (Ferrantelli et al. 2003). Combinations of MAbs were capable of providing protection from infection or from disease progression after oral challenge with different virus strains in neonate macaques. Passive immunisation was effective as pre-exposure prophylaxis, but also as post-exposure prophylaxis when administered up to 12 hours after virus exposure (Ferrantelli et al. 2003). Passive immunisation was studied in adult and neonatal macaques, including protection against different routes (i.v. or oral), different strains of SHIV (SHIV-vpu+, SHIV89.6P, or C clade SHIV-1157ip), as well as different dose-schedules of human MAbs in triple or quadruple combinations. The goal of these animal studies was to develop a safe and effective approach to prevent mother-to-infant transmission of HIV with passive immunisation. Experiments focused on prevention of intrapartum and postnatal virus transmission through breast milk, two of the three recognised modes of maternal HIV transmission.

Taken together, challenge experiments in new-born monkeys resulted in 22 out of 31 neonates completely protected against infection. Table 3-2 summarises the results of passive immunisations using different combinations of the antibodies C4E10, C2F5, and C2G12 in the neonate macaque/SHIV-challenge model.

Passive immunoprophylaxis against SHIV challenge with combinations of C4E10, C2F5, and C2G12 was clearly shown to be :

- safe in neonate and adult rhesus monkeys
- efficient in neonatal rhesus monkeys against oral clade B SHIV challenge after i.v. antibody administration
- efficient in neonatal rhesus monkeys against oral clade C SHIV challenge after i.v. antibody administration
- efficient in neonatal rhesus monkeys against oral clade B SHIV challenge after i.m. antibody administration
- efficient in neonatal rhesus monkeys as prophylaxis and as post-exposure prophylaxis against oral SHIV challenge.

**Table 3-2: Passive immunization against oral SHIV challenge in neonatal macaques**

| MAbs combinations                 | Dose (route) and time of                        | SHIV challenge (AID50) | Monkeys protected/ treated | Reference          |
|------------------------------------------|--------------------------------------------------------|------------------------------------------|-----------------------------------|---------------------------|
| 2G12+2F5+F105                            | 10 mg/kg (i.v.)
5d before birth, d0, d8             | SHIV-vpu + (10x)              | 4/4                               | Baba et al 2000           |
| 2G12+2F5+F105                            | 10 mg/kg (i.v.)
d0, d8                              | SHIV-vpu + (10x)              | 2/2                               | Hofmann et al 2001; 2002a |
| 2G12+2F5+F105                            | 10 mg/kg (i.v.)
PEP i : +1h, d8          | SHIV-vpu + (10x)              | 2/2                               | Hofmann et al 2002a       |
| 2G12+2F5+b12                             | 10 mg/kg (i.v.)
d0, d8                              | SHIV89.6P (15x)                          | 1/4                               | Hofmann et al 2001        |
| 2G12+2F5+4E10 + b12                      | 30 mg/kg (i.v.)
PEP i : +1h, d8          | SHIV89.6P (15x)                          | 2/4                               | Ferrantelli et al 2003    |
| 2G12+2F5+4E10 + b12                      | 30 mg/kg (i.v.)
PEP i : +1h, d8 +12h, d8 | SHIV89.6P (15x)                          | 3/4
1/3                        | Ferrantelli et al 2007    |
| 2G12+2F5+4E10 + b12                      | 30 mg/kg (i.v.)
PEP i : +1h, d8          | SHIV-1157ip (15x)                        | 3/4                               | Xu et al unpublished      |
| 2G12+2F5+4E10                            | 40 mg/kg (i.m.)
PEP i : +1h, d8          | SHIV89.6P (15x)                          | 4/4                               | Ferrantelli et al 2004    |
| Total protected neonatal macaques |                                                        |                                          | 22/31                      |                           |

iPEP: post exposure prophylaxis

### 3.3.2 Pharmacokinetics of Mabgel after single vaginal application to macaques

Two studies were performed in the CEA animal facilities (Fontenay-aux-Roses, France). Six adult, female *Macaca fascicularis* received vaginally 2 g of antibody gel containing 20 mg C2F5, 20 mg C2G12 and 20 mg C4E10 per g.

In the first study animals were dispatched in three groups of two animals (one per time-point). Weck-Cel sampling followed by vaginal lavage was performed after 1 hour (group 1), 4 hours (group 2), 12 hours (group 3) to quantify C2F5, C2G12 and C4E10 antibodies. Blood was drawn 1, 4, 12 and 72 hours after application for quantification of antibodies in serum. Morbidity/mortality, local tolerance, rectal temperature and body weight were recorded. Vaginal application of 120 mg antibody in total was tolerated without adverse events by all animals. Weck-Cel sampling and lavages resulted in similar estimates for antibody concentration at the vaginal mucosa (Figure 3-1). Low quantities (nanogram range) of C2F5 and C4E10 were detected in the serum, whereas C2G12 was not detectable.

[figure not shown]

**Figure 3-1 : Antibody concentrations in lavages obtained 1, 4 and 12 h after vaginal application of Mabgel to macaques**

In the second study the same 6 adult, female *Macaca fascicularis*, after a washout period of 4 days, again received vaginal administration of 2 g of antibody gel containing 20 mg C2F5, 20 mg C2G12 and 20 mg C4E10 per g gel. Weck-Cel sampling was performed in all animals at 1, 4, 8, 12, 24, 48 and 72 hours to quantify C2F5, C2G12 and C4E10 antibodies. Morbidity/mortality, local tolerance, rectal temperature and body weight were recorded.

The second vaginal application of 120 mg antibody in total was again tolerated without adverse events by all animals. All three antibodies were detectable until 72 h with significant quantities (microgram range) detected until 24 h after application (Figure 3-2).

[figure not shown]

**Figure 3-2: Antibody concentrations in wick samples obtained up to 24h after vaginal application of Mabgel to macaques**

### 3.4 Clinical research in human subjects

To date, C2F5, C2G12, and C4E10 have undergone testing in four clinical trials. These have evaluated the safety and efficacy of passive immunotherapy in a total of 39 HIV-1 infected subjects, receiving a total of 418 intravenous antibody infusions. Subjects received between 4 and 16 infusions of each monoclonal antibody at weekly intervals in doses ranging from 1 to 5G per infusion.

**Table 3-3: Overview of clinical trials using C2F5, C2G12, and C4E10 to date**

|                          | Study                                 |                                       |                               |                                     |
|--------------------------|---------------------------------------|---------------------------------------|-------------------------------|-------------------------------------|
|                          | 1
Armbruster
2002  | 2
Armbruster
2004  | 3
Trkola 2005  | 4
Mehandru
2006  |
| No. patients             | 7                                     | 8                                     | 14                            | 10                                  |
| Male/Female              | 4/3                                   | 4/4                                   | 10/4                          | 10/0                                |
| MAbs                     | C2F5, C2G12                           | C2F5, C2G12,
C4E10                 | C2F5, C2G12,
C4E10         | C2F5, C2G12,
C4E10               |
| Dose per infusion (G)    | 1/1                                   | 1/0.5/1                               | 1.3/1/1                       | 1/1/1 (6 pts.)
2/1/2 (4 pts.)    |
| No. infusion days        | 8                                     | 4                                     | 13                            | 16                                  |
| Length of dosing         | 4 weeks                               | 4 weeks                               | 13 weeks                      | 16 weeks                            |
| SAEs                     | 0                                     | 0                                     | 0                             | 0                                   |
| Thrombotic complications | 0                                     | 0                                     | 0                             | 0                                   |
| Possible ADRs            |                                       |                                       |                               |                                     |
| None                     | 7/7                                   | 8/8                                   | 7/14                          | 7/10                                |
| Myalgia                  | 0                                     | 0                                     | 5/14                          | 3/10                                |
| Arthralgia               | 0                                     | 0                                     | 4/14                          | 1/10                                |
| Skin rash                | 0                                     | 0                                     | 1/14                          | 1/10                                |

The results of these trials are detailed in the Investigator's Brochure. In summary, no serious adverse events (SAEs) or thrombotic complications were reported, and very few possible adverse drug reactions (ADRs) were observed. The most common adverse events reported were myalgia, arthralgia, and skin rash. These were generally mild and resolved during or shortly after cessation of dosing. Direct evidence was obtained that these monoclonal antibodies contributed to the temporary containment of HIV-1 replication in infected humans.

Further analyses and experiments in relation to these clinical trials were recently reported, which investigated the possibility of autoreactivity and possible thromboembolic disorders associated with C4E10 and C2F5. During trial 4 (as above table) the study design was modified to collect prospective data from the last four high-dose patients. Very mild (<1.25 x ULN) prolongation of the APTT 30 minutes post-infusion was observed which rapidly remitted, and there was no effect on the PT. In vitro experiments indicated that the effect on coagulation profile was mediated by 4E10. Further analyses indicated that C4E10, but not C2F5, also showed low-level cross-reactivity with cardiolipin, and that infusion of C4E10 resulted in transient low anti-cardiolipin antibody titres. It was concluded that there was little evidence that the monoclonal antibodies conferred an increased risk of thrombosis, but that monitoring of both coagulation parameters and anti-phospholipid antibodies should be carried out in any further clinical trials.

### **3.5 Rationale for study objectives**

This trial is being conducted to assess the pharmacokinetics and safety of the monoclonal antibody combination when applied vaginally. As the antibodies have already been given systemically to HIV infected men and women without any serious adverse events, and the gel formulations using the same components are sold as over-the-counter products (Replens® vaginal lubricant), we have every expectation that the IMP will be safe when applied vaginally.

The primary objective of the study is therefore to understand the pharmacokinetics of the antibody combination when applied vaginally, as this will guide us in terms of future development of the monoclonal antibody combination. Specifically we need to know how long the antibodies persist in the lower female genital tract, as this will inform recommended dosing frequency for development of the microbicide. The a priori hypothesis is that the monoclonal antibodies will not be systemically absorbed because of their relatively large molecular weight. No systemic absorption was detected after repeated application to rabbits. However, recent data in macaques shows very low (nanogram range) systemic absorption of the antibodies when applied vaginally, so this provides the rationale to study this directly in healthy females. We will also monitor systemic and local safety parameters, including haematology, biochemistry and genital adverse events. The formal list of outcome measures is presented in section 5.5.

In summary, administration of C2F5, C2G12, and C4E10 to male and female HIV-infected patients has been judged to be safe and well-tolerated by the investigators in all human clinical trials conducted to date and there are no overt safety concerns with regard to vaginal administration of the MABs to healthy, sexually abstinent female volunteers. The primary objective of this study is to assess the persistence of the MABs in the vagina and the systemic absorption at two different doses.

## **4. STUDY OBJECTIVES**

The primary objective of the study is to assess the pharmacokinetics of the specified monoclonal antibody combination when applied vaginally. Specifically:

- to assess the retention of the MAbs in the vagina after administration of the IMP
- to investigate whether there is any systemic absorption of the MAbs

The secondary objective of the study is:

- to assess the safety of the specified monoclonal antibody combination when applied vaginally

Further exploratory objectives of the study are:

- to investigate the changes in vaginal flora between the placebo and IMP groups after 12 daily doses of the study gel
- to compare self-sampled vaginal secretions to clinician-sampled vaginal secretions
- to investigate participants' experience of taking part in the clinical trial

## 5. STUDY DESIGN

### 5.1 Study Centre

The study will be carried out at York Hospitals NHS Foundation Trust. All visits will take place at York Hospital in conjunction with staff from the HYMS EMU.

### 5.2 Type of design

The study is a double-blinded, randomised, three-arm clinical trial to assess the pharmacokinetics of C2F5, C2G12, and C4E10 monoclonal antibodies (MAbs) when administered together in a gel vehicle as a vaginal microbicide.

### 5.3 Disease/participants studied

Healthy, HIV-negative, women aged  $\geq 18$  and  $\leq 45$  years who will remain sexually abstinent during the study dosing period, but are both willing and able to adhere to the trial conditions, methodology and to give written informed consent. For more details refer to section 6.

### 5.4 Trial interventions – research and control

Participants will receive vaginal microbicide gels containing either (a) high-dose monoclonal antibodies (b) low dose monoclonal antibodies, or (c) a control placebo vaginal microbicide gel. Gels containing either the high or low dose MAbs are referred to as 'the IMP' in this protocol; when referring to either the IMP or the placebo, the term 'study gel' is used. For more details of the study gels refer to section 8. A placebo arm is included in the study to increase the validity of safety endpoint analyses and investigate the impact of the IMP on vaginal flora (see sections 5.5.2 and 12.1).

### 5.5 Outcome measures

#### 5.5.1 Primary endpoint:

- levels of MAbs in Weck-Cel vaginal secretions 1, 8 and 24 hours post-1st dose, 12 & 36 hours post-12th dose

#### 5.5.2 Secondary endpoints:

- 24 hours post-1st dose, and 36 hours post-12th dose cervico-vaginal lavage MAb levels
- 24 hours post-1st dose, and 36 hours post-12th dose Mab levels in self-sampled vaginal aspirate
- 8 hours post-1st dose, and 12 hours post-12th dose serum MAb levels
- Number of grade 3 or above genital adverse events (see Appendix 6) during the dosing or follow up period
- Number of grade 3 or above other clinical or laboratory adverse (see Appendix 7) events confirmed at examination or on repeat testing respectively during the dosing or follow up period
- Number of events attributable to the study gel leading to discontinuation of gel

Data on local events listed above will be solicited with specific questions and/or cervico-vaginal and colposcopic examination. Data on laboratory events will be collected through the routine tests or in response to a clinical event. Data on other events will be collected with open questions. Detail on the analysis of MAbs in vaginal secretions and serum samples can be found in section 10.4.

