| INTERVENTIONS      | Vaginal microbicide gel: (a) high-dose monoclonal antibodies (50mg each of C2F5, C2G12 and C4E10) (b) low dose monoclonal antibodies (25mg each of C2F5, C2G12 and C4E10) or (c) a control placebo vaginal microbicide gel.                                                                                                                                                                                                                                                                                                                                                                                                                                                                                                                                                                                                                                                                                                                                                                                                           |
| OUTCOME MEASURES   | 
Primary endpoint:
 
 
• levels of MABs in Weck-Cel vaginal secretions 1, 8 & 24 hours post-1st dose and 12 & 36 hours post-12th dose
 
 
Secondary endpoints:
 
 
• 24 hour post-1st dose and 36 hours post-12th dose cervico-vaginal lavage MAB levels
 
• 24 hour post-1st dose and 36 hours post-12th dose Mab levels in self-sampled vaginal aspirate
 
• 8 hours post-1st dose and 12 hour post-12th dose serum MAB levels
 
• Number of grade 3 or above genital adverse events during the dosing or follow up period
 
• Number of grade 3 or above other clinical or laboratory adverse events confirmed at examination or on repeat testing respectively during the dosing or follow up period
 
• Number of events attributable to the study gel leading to discontinuation of gel
 
 |

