| Day of menstrual cycle
(Day 1 = first day of bleeding) |                                       | 1               | 7-13
W-Th                | 7-13,
W-Th                       | 7-13,
W-Th                         | 8-14,
Th-Fr                         | 8-16 | 11-19
M-T | 14-22 | 19-25                                   | 20-26                                   | 1               | 7-21 |
| Study day relative to first dose                          |                                       | -42 to -14      | -6 to -12                   | 1                                   | 1                                     | 1                                      | 2    | 2-4          | 5-7   | 8-10                                    | 13                                      | 14              |      |
| Time of visit                                             |                                       |                 | pre-1 st
dose | 1hr
post-1 st
dose | 8 hrs
post-1 st
dose | 24 hrs
post-1 st
dose |      |              |       | 12 hrs
post-12 th
dose | 36 hrs
post-12 th
dose |                 |      |
| Informed Consent                                          |                                       | x               |                             |                                     |                                       |                                        |      |              |       |                                         |                                         |                 |      |
| Randomisation                                             |                                       |                 |                             | x                                   |                                       |                                        |      |              |       |                                         |                                         |                 |      |
| Medical & other history                                   |                                       | x               |                             |                                     |                                       |                                        |      |              |       |                                         |                                         |                 | x    |

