| Pharmacokinetic parameters (for MABs)                     | Serum sample e             |                 |                             | x                                   |                                       | x                                      |      |              |       | x                                       |                                         |                 |      |
|                                                           | Vaginal self-sample e      | x               |                             |                                     |                                       | x                                      |      |              |       |                                         | x                                       |                 |      |
|                                                           | Vaginal Weck-Cel e         |                 |                             | x                                   | x                                     | x                                      |      |              |       | x                                       | x                                       |                 |      |
|                                                           | CVL supernatant & pellet f |                 |                             | x                                   |                                       | x                                      |      |              |       |                                         | x                                       |                 |      |
| Vaginal swab for vaginal flora substudy g      |                                       | x               |                             |                                     |                                       |                                        |      |              |       |                                         | x                                       |                 | x    |
| Side-effect, compliance check                             |                                       |                 |                             |                                     |                                       |                                        | x    | x            | x     | x                                       |                                         |                 |      |

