### **7.3 Visit 3, 8 hours post 1st dose**

The participant will return to the clinical unit for visit 3 eight hours after administration of the first dose. Investigations will be carried out according to the study schedule. The Clinical Investigator will enter the data collected into the participant's file and send all samples for processing and storage at HYMS EMU, or at IIU, York.

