### **7.4 Visit 4, 24 hours post 1st dose**

Twenty-four hours after administration of the first dose, investigations will be carried out according to the study schedule. The Clinical Investigator will enter the data collected into the participant's file and send all samples for processing and storage at HYMS EMU, or at IIU, York.

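### The serum endpoint is set at 8 hours after dose 1, but Table 7-1, as it reads here, takes serum at 24 hours and not at 8 hours

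*Protocol*

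**What the plan says.** The endpoint appears twice in the protocol with the same hours. Section 5.5.2 has "8 hours post-1 st dose, and 12 hours post-12 th dose serum MAb levels"; the outcome measures in Section 1 have "8 hours post-1 st dose and 12 hour post-12 th dose serum MAB levels".

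In the pharmacokinetic block of Table 7-1, the row "Serum sample e" carries three marks, under visits 2, 4 and 6. The visit 3 column, timed "8 hrs post-1 st dose", is empty in that row. The visit 4 column, timed "24 hrs post-1 st dose", is marked.

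The visit descriptions add nothing to the table. Section 7.3 says "The participant will return to the clinical unit for visit 3 eight hours after administration of the first dose" and then "Investigations will be carried out according to the study schedule". Section 7.4 treats visit 4 in the same way: "Twenty-four hours after administration of the first dose, investigations will be carried out according to the study schedule". Neither lists samples.

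Three other places bear on the point:
- Section 7.1.2 allows one hour either side for visits 3, 4, 6 and 7, and has the actual time of each pharmacokinetic sample recorded.
- Section 4 makes systemic absorption one of the two named parts of the primary objective.
- Section 10.2.2 summarises serum levels by group at each time-point and compares the groups.

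**The concern.** A sampling schedule has to produce the data that the endpoints need. Here the endpoint names an hour at which the schedule, as it reads, draws no blood at all: at visit 3 the table marks only the cervico-vaginal examination, colposcopy and the Weck-Cel sample. Because Section 7.3 leaves the content of the visit to the table, staff working from the protocol would have no reason to take serum then.

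Serum is the direct measure of systemic absorption, and it has only two defined post-dose times. Section 3.5 gives low (nanogram-range) absorption in macaques as the reason for measuring it in women. A sample not taken at 8 h cannot be recovered afterwards, and the report would have to explain why a listed endpoint has no data at its first time-point.

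**Working it through.** No power or sample size formula is involved. The check sets the table against the endpoints.

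**1. Fix the columns.** The visit-number row of Table 7-1 has 12 data columns. Counting from the left, column 1 is visit 1, column 3 visit 2, column 4 visit 3, column 5 visit 4, column 9 visit 6 and column 10 visit 7. The time row puts 8 h in column 4, 24 h in column 5, 12 h after dose 12 in column 9 and 36 h in column 10.

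**2. Compare each pharmacokinetic row with its endpoint (Sections 5.5.1 and 5.5.2).**

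| Row | Columns marked | Visits | Post-dose hours in the endpoint | Agreement |
|---|---|---|---|---|
| Weck-Cel | 3, 4, 5, 9, 10 | 2, 3, 4, 6, 7 | 1, 8, 24; 12, 36 | yes |
| Lavage | 3, 5, 10 | 2, 4, 7 | 24; 36 | yes |
| Self-sample | 1, 5, 10 | 1, 4, 7 | 24; 36 | yes |
| Serum | 3, 5, 9 | 2, 4, 6 | 8; 12 | 12 h yes, 8 h no |

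Three rows read correctly only if column 5 is the 24-hour visit. Read in the same way, the serum row gives 24 h where its endpoint says 8 h.

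**3. Test the column reading against the other header rows.**
- The cycle-day row gives column 5 as days 8–14, Thursday to Friday. That is the day after dosing on days 7–13, Wednesday to Thursday, so it is visit 4.
- The study-day row disagrees: it puts day 1 in column 5. The same row puts days 2–4 under visit 5, whereas Section 7.7 places visit 5 on the day of the 5th to 7th dose, and Section 7.6 places the first telephone call on the day of the 2nd to 4th dose. The study-day row is therefore displaced by one column at this point and cannot be used to date column 5.

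**4. Can the visit 4 sample count as the 8-hour sample?**
- Visit 3 window: 8 − 1 = 7 h to 8 + 1 = 9 h.
- Visit 4 window: 24 − 1 = 23 h to 24 + 1 = 25 h.
- Gap between the windows: 23 − 9 = 14 h. It cannot.

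The visit 2 mark is either pre-dose or 1 h after the dose. The text does not show which, but neither is 8 h.

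**5. Size.** Section 6.3 gives 30 women and Section 10.3.1 allocates them 1:1:1.
- Women on active gel: about 30 × 2/3 = 20.
- Results informative on absorption at this time-point: 20 × 3 antibodies = 60.
- Share of the defined post-dose serum times affected: 1 of 2.

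**The case against.** The strongest objection is that the conflict rests on cell positions in a table that has visibly lost a column. Section 7.1.2 gives visit 2 both a pre-dose and a 1-hour sample, so 13 data columns would be expected, and the text shows 12. The header rows do not all lose the column at the same place. If the serum row had dropped one of the blank cells between visit 4 and visit 6, its marks would fall at pre-dose, 8 h and 12 h after dose 12, which is exactly what the endpoint requires. That only the serum row disagrees does not rule this out, since a slip confined to one row would produce just that pattern.

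This stands as a reason for caution and for checking the original table. It is still the less likely reading. The visit-number, time and cycle-day rows and three sample rows place column 5 at 24 h. The APTT/aCL row has the same dosing-cycle marks as serum (columns 3, 5 and 9), so the slip would have had to occur in both blood rows and in none of the other pharmacokinetic rows. The APTT/aCL row has no stated endpoint hour of its own, however, so it supports the reading without proving it.

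The objection is also right about size. A reader might infer that 90 results in all 30 women are at stake, but the placebo gel contains no antibody. A reader might also infer that a 24-hour value would be reported as an 8-hour one. The protocol does not support that, because actual sampling times are recorded.

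**Conclusion.** The concern holds with moderate confidence. As Table 7-1 reads, it contradicts Sections 1 and 5.5.2 on the first-dose serum time, and no other section supplies an 8-hour draw. If the schedule is followed, one of the two defined post-dose serum times has no value at its stated hour, affecting about 20 women on active gel and 60 assay results.

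The conclusion rests on two assumptions: that column 5 of the serum row is visit 4, and that allocation is close to 1:1:1.

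It would go too far to infer that the absorption part of the primary objective is lost. Samples at 24 h after dose 1 and 12 h after dose 12 would still bear on whether any antibody reaches the blood. The primary endpoint, Weck-Cel levels, is fully covered by the schedule. The documents do not show which hour was intended, so this is an internal inconsistency to be reconciled, not evidence that either hour is wrong.

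**What to change.** First compare the serum row, and the APTT/aCL row with it, with the original layout of Table 7-1. If serum is marked at visit 3 there, nothing needs to change.

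If the conflict is confirmed, make Sections 1 and 5.5.2 and Table 7-1 name the same hour before the first dose. There are two ways to do so:
- mark serum at visit 3, which adds at most one blood tube per woman at a visit that already takes place; or
- restate the endpoint at 24 h in Sections 1 and 5.5.2, which adds no sampling.

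Whichever is chosen, the amendment should also say whether the visit 2 serum sample is pre-dose or 1 h after the dose if the original table leaves that open. The check takes minutes, and the correction is a short protocol amendment.
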